# BiCyCLE NMES—neuromuscular electrical stimulation in the perioperative treatment of sarcopenia and myosteatosis in advanced rectal cancer patients: design and methodology of a phase II randomised controlled trial

**DOI:** 10.1186/s13063-021-05573-2

**Published:** 2021-09-15

**Keywords:** Advanced rectal cancer, Sarcopenia, Myosteatosis, Rehabilitation, Exenteration surgery, NMES, Neuromuscular electrical stimulation

## Abstract

**Background:**

Colorectal cancer is associated with secondary sarcopenia (muscle loss) and myosteatosis (fatty infiltration of muscle) and patients who exhibit these host characteristics have poorer outcomes following surgery. Furthermore, patients, who undergo curative advanced rectal cancer surgery such as pelvic exenteration, are at risk of skeletal muscle loss due to immobility, malnutrition and a post-surgical catabolic state. Neuromuscular electrical stimulation (NMES) may be a feasible adjunctive treatment to help ameliorate these adverse side-effects. Hence, the purpose of this study is to investigate NMES as an adjunctive pre- and post-operative treatment for rectal cancer patients in the radical pelvic surgery setting and to provide early indicative evidence of efficacy in relation to key health outcomes.

**Method:**

In a phase II, double-blind, randomised controlled study, 58 patients will be recruited and randomised (1:1) to either a treatment (NMES plus standard care) or placebo (sham-NMES plus standard care) group. The intervention will begin 2 weeks pre-operatively and continue for 8 weeks after exenterative surgery. The primary outcome will be change in mean skeletal muscle attenuation, a surrogate marker of myosteatosis. Sarcopenia, quality of life, inflammatory status and cancer specific outcomes will also be assessed.

**Discussion:**

This phase II randomised controlled trial will provide important preliminary evidence of the potential for this adjunctive treatment. It will provide guidance on subsequent development of phase 3 studies on the clinical benefit of NMES for rectal cancer patients in the radical pelvic surgery setting.

**Trial registration:**

Protocol version 6.0; 05/06/20. ClinicalTrials.gov NCT04065984. Registered on 22 August 2019; recruiting.

**Supplementary Information:**

The online version contains supplementary material available at 10.1186/s13063-021-05573-2.

## Background

Radical multi-visceral resection of pelvic tumours, known as pelvic exenteration, is being utilised to successfully treat a number of intra-abdominal malignancies [1]. Pelvic exenteration for locally recurrent (LRRC) or primary advanced rectal cancer has a high morbidity and mortality. The *PelvEx Collaborative* analysed data from 1184 patients, who underwent surgery for LRRC, and found that 2% of patients died within 30 days of surgery and 32% of patients experienced a major complication [2]. Despite this high morbidity and mortality, these complex procedures are increasingly practised in specialist centres. Following surgery, these patients enter a catabolic crisis where incapacitation and high protein and fat metabolism lead to a marked loss in skeletal muscle [3–5]. Low skeletal muscle mass (sarcopenia) and fatty infiltration (myosteatosis) are independently associated with poorer post-operative outcomes following surgery for colorectal cancer [6, 7]. The aetiology behind sarcopenia and myosteatosis is complex and multifactorial and includes inflammatory changes, hormonal changes, loss of function, fatigue and energy balance [8]. However, strategies to preserve skeletal muscle mass, quality and function may improve these outcomes.

A meta-analysis of resistance exercise training in patients with non-metastatic cancer showed significantly increased skeletal muscle mass [9]. Exercise can also impart an anti-inflammatory effect by attenuating the cellular response to inflammatory stimuli and pro-inflammatory cytokines such as IL-6, TNFα and TGFβ [10, 11]. However, exercise programmes following a rectal cancer diagnosis and exenterative surgery are not always possible or practical due to patient anxieties and the need to expedite treatment, and the pain or disability associated with the extensiveness of the surgery itself. Furthermore, restriction upon rehabilitative resources, especially physiotherapy, often leaves patients immobile for long periods with resultant muscle atrophy. An alternative approach to traditional physiotherapy could be functional electrical stimulation (FES) via neuromuscular electrical stimulation (NMES). This is currently used in clinical practice for a number of diseases, indeed, at the National Clinical FES Centre at Salisbury, UK, over 2500 patients are currently undergoing FES [12]. NMES of the lower-limb muscles requires less motivation than traditional exercise and can be undertaken whilst the patient is seated or lying down [13]. NMES can be used to produce a muscle contraction equivalent to 20 to 40% of a maximum voluntary contraction [14] thus meeting the criteria of the American College of Sports medicine definition of planned exercise [15].

A study of anterior cruciate ligament [of the knee] (ACL) reconstruction patients by Hasegawa and colleague demonstrated NMES, implemented during the early rehabilitation stage, was effective in maintaining and increasing muscle thickness and strength in the operated limb [16]. There is also evidence from meta-analyses that NMES increases muscle strength and shows potential benefit for joint range of motion, muscle atrophy, outcomes of ventilation and activity limitations in critically ill patients [17]. A Cochrane review of NMES in a number of diseases that cause cachexia (muscle and fat loss secondary to disease) such as COPD (Chronic obstructive pulmonary disease), CCF (Congestive cardiac failure), HIV/AIDS and cancer, suggested that NMES may be an effective treatment for muscle weakness in adults with advanced progressive disease, and could be considered as a treatment within rehabilitation programmes [18]. Two studies, a phase 2 randomised trial and its pilot study, investigated NMES in cancer cachexia. Both studies were conducted in patients with non-small cell lung cancer receiving palliative chemotherapy [13, 19]. The pilot study [19] demonstrated positive results however, in the phase 2 study of 49 patients, in which 30 were randomised to NMES, there were no significant differences in quadriceps muscle strength, thigh lean mass or physical activity level between groups [13]. The study team did however recommend further NMES studies in patients with cancer in other settings. Notably these two studies by Maddocks’ and colleagues focussed on palliative lung cancer patients; a surgical complex rectal cancer cohort is fundamentally different both by virtue of the impact of the insult of surgery on muscle but also the radical or curative nature of the treatment. The differences between these studies by Maddocks et al. and our study are summarised in Table 1.

**Table 1 Tab1:** Differences between BiCyCLE NMES and earlier studies by Maddocks et al.

BiCyCLE NMES study population	Maddock’s study population
Post-operative “tumour free”	Active cancer
Confined to bed rest	Active and mobile population
Intensive inpatient support	Outpatient community care
Aiming for recovery up to or beyond baseline	Palliative and functionally declining population

Previous studies have examined NMES is the palliative setting, with inconclusive conclusions regarding efficacy [13, 19]. No work has yet been done on clinical outcomes of NMES use in colorectal cancer nor any trial in the post-operative setting for cancer surgery. A phase II trial is required to determine whether there is evidence of a potential benefit prior to justifying a phase III study. The previous studies performed in cancer patients have not examined the relationship to the systemic inflammatory response, nor has there been an assessment of immediate post-operative outcomes. Our study aims to provide evidence of early indicative evidence of efficacy in relation to key health outcomes, including skeletal muscle mass and quality (myosteatosis), markers of systemic inflammation and post-operative recovery outcomes in rectal cancer patients undergoing radical pelvic surgery.

## Study design, methods and analysis

The study is being undertaken at St Mark’s Hospital, the sponsor in London North West University Healthcare (LNWH) NHS Trust. Details of the study sponsor and their roles and responsibility including auditing, indemnity and monitoring can be found in the full trial protocol provided as supplementary material, (page VIII and pages 24-26). Detailed information relating to the trial authors, management teams and committees including their roles and responsibilities can be found in the supplementary material full trial protocol under the relevant headings. Any amendments will be processed and communicated through the NHS Health Regulation Authority, Queens Square Research and Ethics committee and LNWH Research and Development Department, see Full Protocol pages 24–25 for further details.

Patients will be blinded as to which trial arm they enter and a sham protocol will be used by the control arm. Body composition analysis of the images will be done by automated software used by an assessor blinded to the intervention to remove operator or interpretation bias.

Our aim is to compare the effect on muscle of therapeutic NMES and current best practice against placebo NMES and current best practice alone in patients undergoing advanced radical surgery for complex rectal cancer.

### Outcomes

#### Primary outcome

The difference in mean muscle attenuation (MA), of all skeletal muscle groups captured on the axial CT image at the level of the third lumbar vertebrate (L3), measured in Hounsfield units and hence the degree of myosteatosis between the pre-operative and 6-month post-operative CT scan in the NMES treatment group and the placebo NMES group.

#### Secondary outcomes

Our main secondary outcomes include change in total skeletal muscle cross-sectional area, at the L3 level between treatment and non-treatment groups as well as between time points for individual patients. Difference in quality of life between groups using the validated questionnaires ED-5Q-5L & EORTC QLQ – CR29. Post-operative complications and length of hospital stay between both arms and comparison of the systemic inflammatory response between each group. A comprehensive list of secondary outcomes is shown in Table 2.

**Table 2 Tab2:** Secondary outcomes

Domain	Specific measurement	Metric	Method of aggregation	Time point
Lumbar skeletal muscle index (LSMI)	The difference in lumbar skeletal muscle index (LSMI=height / area of skeletal muscle in cm^2^ at L3) derived from the third lumbar vertebral axial level	Change in LSMI at each time point	CT Scan; SliceOmatic software version 5.0 with ABACS L3 Plug-in automation tool	Pre-surgery 3 to 6 months post-surgery
Visceral adipose tissue (VAT) Surface area	Visceral adipose tissue area (cm^2^) derived from the third lumbar vertebral axial level	Change in VAT at each time point	CT Scan; SliceOmatic software version 5.0 with ABACS L3 Plug-in automation tool	Pre-surgery 3 to 6 months post-surgery
Systemic inflammation	C-Reactive Protein and serum albumin	Modified Glasgow Prognostic Score	Ordinal values mGPS=0 mGPS=1 mGPS=2	Preoperatively and 6 months post-surgery
Cellular immune response	Neutrophil count Lymphocyte count	Neutrophil to lymphocyte ratio (neutrophil/lymphocyte count	Clinically relevant categorical cut off values NLR<3 NLR>3	Pre-operatively and 6 months post-surgery
Post-operative complications	Any post-operative complication	Clavien-Dindo Classification	Clavien-Dindo Score 1–5	Between 0 and 90 days post-surgery
Length of hospital stay	Inpatient stay post-surgery	Days	Median length of stay	From surgery to hospital discharge
Disease-free survival	Days to reported first recurrence / death / 5 years post-surgery	Days	Kaplan-Meier survival analysis	From date of surgery to 5 years post-surgery
Overall survival	Days to death / 5 years post-surgery	Days	Kaplan-Meier survival analysis	From date of surgery to 5 years post-surgery
Quality of life (General)	EuroQol 5-level EQ-5D5L Mobility, self-care, usual activities,	Visual analogue scale score 1–100 and score in each of the 5 domains	Change in scores between events	Pre-surgery, 6 and 12 months post-surgery
	Pain/discomfort and anxiety/depression			
Quality of life (colorectal specific)	EORTC QLQ - CR29 Function and Symptoms	4 multi-item scales and 19 single items assessing common symptoms and problems in colorectal cancer	Change in score between events	Pre-surgery, 6 and 12 months post-surgery
Function	Berg Balance Scale (BBS)	Berg balance score (0–56)	Change in BBS score	Pre-surgery and 6 months post-surgery
	30 s sit to stand	Number of full sit-to stand actions completed in 30 s	Change in number of successful actions	
	6-min walk test	Distance walked in 6 minutes	Change in metres	
Thigh circumference	Thigh circumference, 5cm above the superior pole of the patella	Circumference in cm	Change in thigh circumference between groups	
Dose response to NMES	Pre- and post-operative mean muscle attenuation (L3) (MMA) and hours of device usage	Change in MMA/time	Linear regression	3–6 months post-surgery
Patient satisfaction	Free text responses and satisfaction scores derived from each domain (see patient satisfaction survey supplementary material).	Qualitative and visual analogue scale 1-10	Qualitative responses Median score between groups on each domain assessed	8 weeks post-surgery
Bioimpedance analysis	Phase angle = (Xc/R)*180°/π	Cellular resistance (R) and cellular reactance (Xc)	Change in phase angle at each time point	Baseline, day 2 post operatively, day 28 postoperatively (if in hospital), day of discharge, first post-operative follow-up appointment

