### Planned statistical analyses

This study will be performed in line with the CONSORT criteria (http://www.consort-statement.org/consort-2010). Initially outliers, patterns of attrition and missing data will be identified using a combination of graphical displays and descriptive statistics allowing decisions on the assumption of normality. The primary analysis will be of observed data only, with patients with missing data omitted from the analysis. If the primary outcome has >10% missing data points, a sensitivity analysis will be performed using multiple imputation to estimate the missing values.

Data will be analysed by a statistician blinded to the intervention. Analyses of primary and secondary endpoints will be based on the full analysis set defined according to the intention to treat principle. Safety analysis will be performed for the on all enrolled individuals with disclosure of any significant adverse events. The full analysis set consists of all participants consented and randomised with valid baseline assessments. Participants will be analysed according to the study arm they were assigned at randomisation.

The primary outcome is myosteatosis at 3–6 months post-surgery, derived from the mean muscle attenuation on CT body composition analysis. This will be analysed using analysis of covariance (ANCOVA), with muscle attenuation values at baseline used as a covariate in the analysis.

The secondary outcome measures measured on a continuous scale, and with a baseline measurement will be analysed using equivalent methods as the primary outcome. For continuous outcomes with no baseline measurement, group comparisons will be made using either the unpaired *t*-test or Mann-Whitney test, depending on data distribution. The chi-square test, or Fisher’s exact test, will be used to compare categorical outcomes between the study groups.

Significance will be assumed when *p*<0.05.

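### Post-operative complications are graded Clavien-Dindo 1–5 with no category for an uncomplicated patient and no worst-grade rule, and the only test named for categorical outcomes ignores the order of the grades

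*Protocol article*

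**What the plan says.** In the protocol article, Table 2 (Secondary outcomes) has a row for post-operative complications. The measurement is "Any post-operative complication", the metric is the Clavien-Dindo classification, the aggregation is "Clavien-Dindo Score 1–5" and the window is "Between 0 and 90 days post-surgery". The row does not say what a patient with no complication scores, or which grade counts for a patient with several. The text above the table lists complications among the main secondary outcomes.

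In the same table the modified Glasgow Prognostic Score is set out as "Ordinal values mGPS=0 mGPS=1 mGPS=2": labelled ordinal, and with a zero.

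Planned statistical analyses bases primary and secondary endpoints on all randomised participants with valid baseline assessments, under intention to treat. On tests it says: "The chi-square test, or Fisher’s exact test, will be used to compare categorical outcomes between the study groups". It names the unpaired t-test or Mann-Whitney test for continuous outcomes without a baseline. It names no method for ordered grades and does not say which group the complication score belongs to.

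**The concern.** Two things do not fit together.

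First, the analysis population includes every randomised patient with a valid baseline, but the stated score has values only for patients who had a complication. An uncomplicated patient belongs in the comparison and has no printed value. A patient with two events has two possible values. Whoever runs the analysis must settle both questions, and nothing in the article settles them in advance.

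Second, a five-grade classification with no baseline is most naturally treated as categorical, which sends it to chi-square or Fisher's exact test. Both treat the grades as unordered labels, so a general shift towards milder grades counts for no more than an equally large scatter with no direction. With about 29 patients per arm spread over six categories, that discards much of the information.

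At stake is the power to see a signal in one of the main secondary outcomes of a phase II trial that is meant to guide a phase III design.

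**Working it through.** **The plan's own figure.** The article states no power for this outcome, only for the primary one. That figure reproduces:

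- Adjusted SD = 9.4 × √(1 − 0.3²) = 8.97 HU.
- n per arm = 2 × (1.960 + 1.282)² × 8.97² / 8² ≈ 26.4, so 27 per arm and 54 in total, as stated.
- Dropout: 54 / 0.95 = 56.8, so 57, or 58 to keep the arms equal, as stated.

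Nothing below changes this.

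**Inputs from the article.** 58 patients randomised 1:1 give 29 per arm; the 5% significance level is taken as two-sided. Background reports, for surgery in locally recurrent disease, that "2% of patients died within 30 days of surgery and 32% of patients experienced a major complication".

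**Assumptions (not in the article).** Major means grade 3 or above. The control arm has 32% major complications, including 2% deaths. The uncomplicated share is unknown, so four control distributions were tried. NMES acts as a common (proportional) odds ratio of 2 or 3 towards lower grades.

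Control percentages for grades 0/1/2/3/4/5:

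- A: 25 / 18 / 25 / 20 / 10 / 2
- B: 20 / 19.2 / 28.8 / 22 / 8 / 2
- C: 35 / 13.2 / 19.8 / 22 / 8 / 2
- D: 50 / 7.2 / 10.8 / 22 / 8 / 2

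**What these odds ratios mean.** For each cumulative probability c of being at or below a grade, the treated value is OR·c/(1 − c) ÷ [1 + OR·c/(1 − c)]. For below grade 3, c = 0.68 and the odds are 0.68/0.32 = 2.125.

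- OR 2: 4.25/5.25 = 0.810, so major complications fall from 32% to 19.0%.
- OR 3: 6.375/7.375 = 0.864, so they fall to 13.6%.

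**Simulated power, worst grade 0–5, all 58 patients** (4,000 trials per scenario for A, 2,000 for B–D):

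| Control | OR 2, chi-square | OR 2, Mann-Whitney | OR 3, chi-square | OR 3, Mann-Whitney |
|---|---|---|---|---|
| A (25% none) | 15% | 30% | 35% | 62% |
| B (20% none) | 14% | 29% | 35% | 61% |
| C (35% none) | 14% | 29% | 34% | 59% |
| D (50% none) | 12% | 27% | 26% | 52% |

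Repeat runs moved individual entries by up to about two points (A at OR 3: 36% and 60%; D at OR 2, Mann-Whitney: 26%), hence the rounded ranges used elsewhere.

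**Type I error with no effect.** Chi-square 3.0–3.6%; Mann-Whitney 4.0–4.7%. Both are within the 5% level, so the plan's test is valid. Fisher's exact test was not simulated; it too ignores order.

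Both columns already include the grade 0 category and the worst-grade rule. The table therefore isolates the cost of ignoring order, which is roughly half the power.

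**The case against.** The strongest reply is that this is a condensed article that defers to a full protocol not shown here. The worst-grade rule and the test for one graded outcome may be fixed there or in an analysis plan. The printed range may simply name the grades of a classification of complications, and silence about patients with none is not a rule to drop them. The sentence on categorical outcomes is generic and never mentions Clavien-Dindo. Part of this stands: the use of chi-square or Fisher here is an inference, and the test is valid. It does not dispose of the point. Table 2 states an aggregation rule that does not cover the stated analysis population, and the article names no ordinal method.

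The power figures also depend on assumptions. The background rates come from recurrent disease, while the trial also enrols primary disease. The simulated shift is of the kind that suits a rank test; an effect confined to one grade would show a smaller gain. Even after the change, power for this outcome is modest, and the article says that the trial is powered on the primary outcome only. All of this is correct. It limits the size of the claim, not its direction.

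Three stronger readings are tempting and are not supported:

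- **That only complicated patients are compared, so prevention earns no credit.** The intention-to-treat analysis set keeps uncomplicated patients in, and the row's measurement can be answered no. This is one possible reading of the row, not what the plan says.
- **That length of stay is mis-scored because it ends at discharge.** A rule for death before discharge is missing detail. At the 2% 30-day mortality in Background, about 0.02 × 58 = 1.2 patients would be affected. The summary is a median, deaths are recorded under 30-day and overall survival, and ranking a death as the longest stay is one debatable convention among several.
- **That the trial has no other recovery outcomes.** Table 2 also lists walking, sit-to-stand, balance and quality of life.

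**Conclusion.** The point holds for the complications outcome. The score as printed has no value for a patient without a complication and no rule for several complications in one patient, and the natural reading of the analysis section compares ordered grades with a test that ignores order. That test controls type I error but is inefficient. With 29 per arm, power is about 26–36% instead of 52–62% at an odds ratio of 3, and about 12–15% instead of 26–30% at an odds ratio of 2. These figures rest on assumed grade distributions with 20–50% uncomplicated, on major meaning grade 3 or above, and on a proportional-odds effect.

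This is a worthwhile improvement to a main secondary outcome, not an error that threatens the trial. The primary outcome and the sample size are untouched.

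**What to change.** In Table 2, define the outcome as each patient's worst Clavien-Dindo grade within 90 days of surgery, from 0 (no complication) to 5.

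In Planned statistical analyses, name this outcome and compare arms with a Mann-Whitney test or a proportional-odds model instead of chi-square or Fisher's exact test. Report the proportion at grade 3 or above in each arm descriptively. If the full protocol or an analysis plan already sets these rules, bring Table 2 into line with it.

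The cost is a few lines of wording. Table 4 already lists 90-day complications by Clavien-Dindo among the data to be collected, so no new data are needed. The wording should be fixed before anyone compares the arms.

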#### Data collection

Surveillance CT scans performed as part of sequential screening (i.e. not emergency or non-routine imaging) are performed as standard in this patient group and will undergo analysis measuring mean muscle attenuation (myosteatosis) and muscle area (sarcopenia) at the level of the third lumbar vertebrate. Routine bloods including CEA (carcinoembryonic antigen) and inflammatory markers will be measured at each elective routine clinic visit and these data recorded, these samples will be collected, analysed and disposed of in accordance with the LNWH NHS Trust policy. Quality of life will be assessed at 6 and 12 months using validated quality of life questionnaires (ED-5Q-5L & EORTC QLQ – CR29). The Berg Balance scale, 30-s sit-to-stand test and 6-min walk test [21–24] will be used to assess functional outcome these tests will be performed at the patients 3 months post operatively clinic appointment. Pre- and post-operatively, we will measure bilateral thigh circumference at 15cm above the superior pole of the patella (which has been shown in earlier studies to correlate with muscle volume on MRI) [25]. Bio-impedance analysis (BIA) will be undertaken at baseline, day 2 post-operatively, day 28 post-operatively (if in hospital), day of discharge and first post-operative follow-up appointment. We will record data from the device satisfaction questionnaires from both groups. Standard outcome data and covariates to be collected are shown in Table 4.

**Table 4 Tab4:** Outcomes and covariates

**Demographics** o Patient age o Patent birth year o Patient gender o Patient ethnicity coding o Weight o Height o Body mass index	**Outcome measures** o 90-day post-operative complications (Clavien-Dindo classification (18)) o Disease outcomes including 30-day survival o Death / recurrence / disease-free survival o Patient compliance diary data o Device usage
**Disease** o ASA grade (American College of Anaesthesiology) physical status o Past medical history (other or previous illnesses and surgery)	**Body composition parameters** o CT body composition at the level of the L3 vertebra o Bio-impedance analysis o Anthropometric measurements
**Cancer-specific characteristics** o Type of cancer (primary/recurrent cancer, location and subtype on histology) o Grade of cancer o Stage of cancer	**Inflammatory markers** o Serum C-reactive protein o White cell count o Serum albumin o Platelet count

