#### Anthropometrics and bio-impedance analysis

Bio-impedance analysis (BIA) will be undertaken using a SECA mBCA 525 analyser (*SECA, Hamburg Germany*). This will be performed at baseline, day 2 post-surgery, either hospital discharge or at 28 days post-surgery (whichever is first) and at 6 months. Patients will undergo analysis in a fasted state. Posterior upper arm skin fold thickness and waist circumference will be performed at baseline and 6 months. We will measure thigh circumference at 15cm above the superior pole of the patella (which has been shown in earlier studies to correlate with muscle volume on MRI) [25]. Phase angle from BIA and patient BMI will be utilised as categorical variables with other outcome variables being continuous.

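### Phase angle read at discharge, and at day 28 in inpatients only, makes timing and inclusion depend on length of stay, itself a between-arm outcome

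*Protocol article*

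**What the plan says.** Table 2 (Protocol article, Secondary outcomes) lists bio-impedance at "Baseline, day 2 post operatively, day 28 postoperatively (if in hospital), day of discharge, first post-operative follow-up appointment" and summarises it as "Change in phase angle at each time point". The Data collection section repeats that schedule after baseline: "day 2 post-operatively, day 28 post-operatively (if in hospital), day of discharge and first post-operative follow-up appointment".

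The section Anthropometrics and bio-impedance analysis differs. After baseline and day 2 it has one reading at "either hospital discharge or at 28 days post-surgery (whichever is first) and at 6 months". It also states "Phase angle from BIA and patient BMI will be utilised as categorical variables", whereas Table 2 works with a change in phase angle.

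Length of stay is among the main secondary outcomes, which include "Post-operative complications and length of hospital stay between both arms". Its time frame in Table 2 is "From surgery to hospital discharge".

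Planned statistical analyses puts primary and secondary endpoints on an intention-to-treat full analysis set of randomised participants with valid baseline assessments. Continuous secondary outcomes that have a baseline value are analysed like the primary outcome, by ANCOVA on baseline. Categorical outcomes get a chi-square or Fisher's exact test. Neither the day of measurement nor discharge status is mentioned.

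**The concern.** Two of the Table 2 time points are set by the patient's recovery rather than by the calendar. Discharge fixes when one reading is taken and who contributes to the other. Discharge happens after randomisation, and treatment may affect it.

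If the arms differ in length of stay, the discharge comparison sets readings taken at one average time after surgery against readings taken at another. The day-28 comparison sets the slower recoverers of one arm against a differently selected group of slower recoverers in the other. A difference in phase angle could then appear with no effect of NMES on phase angle. The inpatient day-28 comparison also cannot be made on the full analysis set that the plan prescribes, because the outcome is undefined for everyone already discharged.

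**Working it through.** **The plan's own figures.** There is none for phase angle. The only sample-size figure concerns muscle attenuation. With SD 9.4 HU, difference 8 HU, correlation 0.3, two-sided 5% and 90% power, n = 2 × (1.960 + 1.282)² × 9.4² × (1 − 0.3²) / 8² = 26.4, so 27 per group. Then 27 / 0.95 = 28.4, so 29 per arm and 58 in total. This reproduces the plan and is not touched by the point.

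**The schedules side by side.**
- Table 2 and Data collection: the discharge reading has variable timing, and the day-28 reading has variable membership. The first follow-up appointment has no date in the text.
- Bio-impedance section: every patient has one reading at the earlier of discharge and day 28, so nobody is selected out, but timing still varies with stay up to day 28. The 6-month reading does not depend on discharge.
- Baseline and day 2 do not depend on discharge under either schedule.

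**Illustrative size.** The documents give no phase-angle or length-of-stay data, so every input here is an assumption:
- stay is log-normal with log-SD 0.5 and control median 16, 21 or 28 days, and NMES shortens it by 20%;
- change in phase angle at day t is −0.8 + slope × t/7 − 0.4u + noise (SD 0.3), where u is a standard-normal frailty term and the slope is +0.1, 0 or −0.1 degrees per week;
- the correlation of u with log stay is 0 or 0.6;
- NMES has no effect on phase angle.

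The model was simulated with 400,000 patients per arm. Closed forms agree with the results:
- Discharge difference = (slope/7) × difference in mean stay, with mean stay = median × exp(0.5²/2) = median × 1.133. For a median of 21 days: (0.1/7) × (19.0 − 23.8) = −0.07.
- Share in hospital at day 28 = 1 − Φ(c), with c = ln(28/median)/0.5. For a control median of 21, c = 0.575, giving 28%. For NMES (median 16.8), c = 1.022, giving 15%.
- Day-28 inpatient difference = −0.4 × 0.6 × [λ(c NMES) − λ(c control)], with λ(c) = φ(c)/(1 − Φ(c)). For a median of 21: −0.24 × (1.54 − 1.20) = −0.08.

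| Control median stay (days) | Discharge difference, NMES minus control: rising / flat / falling | In hospital at day 28: control / NMES | Day-28 inpatient difference, correlation 0.6 |
|---|---|---|---|
| 16 | −0.05 / 0.00 / +0.05 | 13% / 6% | −0.09 |
| 21 | −0.07 / 0.00 / +0.07 | 28% / 15% | −0.08 |
| 28 | −0.09 / 0.00 / +0.09 | 50% / 33% | −0.07 |

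With correlation 0 the day-28 inpatient difference is about 0. Under the earlier-of-discharge-and-day-28 rule, the difference is about −0.03 to −0.04 if phase angle is rising, about 0 if flat, and +0.03 to +0.04 if falling. Measuring everyone at a fixed day 28 gives 0.00 throughout. The discharge bias is proportional to the assumed slope and to the assumed shortening of stay.

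**Against sampling error.** In this model the SD at a fixed day is √(0.4² + 0.3²) = 0.5. With 29 per arm the standard error of a difference is 0.5 × √(2/29) = 0.13, so a discharge bias of 0.05 to 0.09 is 0.4 to 0.7 of a standard error. At day 28, a control median of 21 days leaves about 29 × 0.28 = 8 control and 29 × 0.15 = 4 NMES patients. The standard error is then about 0.5 × √(1/8 + 1/4) = 0.31, and the bias is about a quarter of it.

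**The case against.** The strongest reply is that Table 2 names no between-arm test at discharge or at day 28, and that choosing which repeated readings to test is normal work for an analysis plan. Phase angle is also one row in a long secondary list of a phase II trial powered on CT muscle attenuation. The scope argument stands. The first argument stands only in part: the article itself fixes these time points as an outcome, and its general rule sends secondary outcomes to between-arm tests on the full analysis set, with no exception for these readings.

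A second reply is that the bio-impedance section already removes the day-28 selection. It does, but it contradicts Table 2 and Data collection and still leaves the timing tied to stay.

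A reader might also infer that an NMES arm that recovers faster would necessarily look worse on phase angle, so that a true benefit would be masked. The documents do not support that. At discharge the sign depends on whether phase angle is rising or falling during the stay, and no trajectory is given. The Background describes marked post-operative muscle loss, which fits a falling course at least as well, and then earlier discharge would flatter NMES. At day 28 the direction needs slower recoverers to have lower phase angle. The Discussion hopes for earlier mobilisation and does not state a shorter stay. The illustrative biases are also smaller than the sampling error, so the inpatient day-28 comparison in particular is more uninformative than misleading.

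**Conclusion.** The point holds as a design weakness in one secondary outcome. Followed as written in Table 2 and Data collection, the discharge comparison has stay-dependent timing and the day-28 comparison has stay-dependent membership. ANCOVA on baseline corrects neither, because both arise after randomisation.

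The direction is open at discharge and conditional at day 28. The size cannot be computed from the documents. About 0.05 to 0.1 degrees for a 20% shorter stay is an illustration resting wholly on assumed values. If the arms do not differ in stay, there is no bias from this source. The primary outcome and the sample size are unaffected. The conflict between the two bio-impedance schedules, and between change and categorical phase angle, needs resolving in any case, since the variable type decides which test applies.

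**What to change.** 1. Reconcile the bio-impedance schedule and the variable type across Table 2, Data collection, and Anthropometrics and bio-impedance analysis, and align Fig. 2 with the result.
2. Limit the between-arm phase-angle comparison to day 2 and the 6-month reading already in the bio-impedance section, each adjusted for baseline. The first follow-up appointment should not stand in for the 6-month reading unless it is given a stated time after surgery.
3. Report the discharge-day and inpatient day-28 readings descriptively, with days since surgery and the number measured per arm, and without between-arm tests.

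This needs wording changes in the protocol and analysis plan, and no measurement beyond those the bio-impedance section already lists. If the schedules were reconciled by dropping the 6-month reading, day 2 would be the only post-operative point with a stated time in all patients, so that reading should be kept. The downside is two fewer formal comparisons.
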